#### Secondary outcome measures

The secondary outcomes aim to estimate retention and the variability of outcome measures and evaluate the acceptability and fidelity of the intervention.

To estimate retention and the variability of outcome measures to inform sample size calculations for a future effectiveness study, completion rates of outcome questionnaires at baseline, three months, and six months post-randomisation will be assessed. These questionnaires will provide comprehensive data on participants’ fatigue levels, coping strategies, functional impairment, symptom responses, and health-related quality of life. Additionally, a comparison between the intervention group and the control group in terms of completion rates and results of questionnaires will be conducted to investigate whether the intervention creates an impact that differentiates the two groups. The questionnaires include the following:

Carver’s Brief Coping Orientation to Problems Experienced (Brief-COPE) inventory [9]The Brief COPE consists of 14 subscales with 2 items per subscale, and categories into 3 dimensions by Cooper et al. [13]: Emotion-focused coping includes acceptance, emotional support, humour, positive reframing, and religion. Problem-focused strategies consist of active coping, planning, and instrumental support. Dysfunctional strategies encompass denial, self-distraction, substance abuse, behavioural disengagement, self-blame, and venting. Each item is rated on a 4-point Likert scale ranging from 1 (“I haven’t been doing this at all”) to 4 (“I’ve been doing this a lot”). It assesses a range of coping responses, including problem-focused coping, emotion-focused coping, and avoidant strategies. Question 6, 8, 11, 13, 16, and 26 are reverse scoring.EuroQoL-5 Dimensions 5 Levels (EQ-5D-5L) [19]The EQ-5D-5L is a standardised instrument assessing five dimensions of health: mobility, self-care, usual activities, pain/discomfort, and anxiety/depression. Each item is rated on a 5-level scale from 1 (no problems) to 5 (extreme problems). Utility scores will be derived using the van Hout et al. [36] crosswalk mapping function. A visual analogue scale (0–100) captures overall self-rated health.Functional Assessment of Chronic Illness Therapy- Fatigue (FACIT-F) [37]The FACIT-F is a questionnaire covering five domains: physical well-being, social/family well-being, emotional well-being, functional well-being, and fatigue. Items are scored on a 5-point Likert scale from 0 (“not at all”) to 4 (“very much”). Subscale scores are summed to produce a total score indicating the degree of fatigue and its impact on daily life. Questions GSs, GFs, An5, An7 are reverse scoring.Prototype F-ACT Scale (adapted version of Inflammatory Bowel Disease- Fatigue Scale) [15]This adapted measure includes: Section I: Fatigue severity (5 items scored 0–4); Section II: Impact on daily activities (25+ items, scored 0–4 with N/A option for question 3, 4, 9, 12, 13, 14); Section III: Additional qualitative questions It captures causes of fatigue, assistance to ease fatigue, as well as duration and frequency of fatigue on physical, cognitive, emotional, and social aspects.Work and Social Adjustment Scale (WSAS) [27]The WSAS is a 5-item scale measuring functional impairment in work, home management, social and private leisure, and relationships. Each item is scored from 0 (“not at all impaired”) to 8 (“very severely impaired”). Higher scores indicate greater functional impairment.Cognitive and Behavioural Responses to Symptoms Questionnaire (Short version) (CBRQ) [30]The short version of the CBRQ consists of 18 items across six subscales: Fear avoidance, Damage beliefs, Embarrassment avoidance, Symptom focusing, All-or-nothing behaviour, Resting behaviour. Each item is rated on a 5-point Likert scale from 0 (“strongly disagree”) to 4 (“strongly agree”). Questions FA2 and FA9 are reverse scoring.

Additionally, to evaluate the acceptability and fidelity of the intervention will be evaluated using a combination of quantitative and qualitative methods six months after randomisation. Participants will complete the Theoretical Framework for Acceptability Questionnaire (TFAQ) [32] and the System Usability Scale (SUS) [5] to assess their perceptions of the intervention and the usability of the digital platform.

Theoretical Framework for Acceptability Questionnaire (TFAQ) [32]TFAQ Comprises: Section 1 (All participants) including 6 items covering affective attitude, burden, ethicality, self-efficacy, opportunity costs, and general acceptability and Section 2 (Intervention group only) including 8 items covering the same plus perceived effectiveness and intervention coherence Responses are on a 5-point Likert scale from 1 to 5.System Usability Scale (SUS) [5]The SUS contains 10 items measuring system usability. Responses range from 1 (“strongly disagree”) to 5 (“strongly agree”). Items alternate between positively and negatively worded statements. Question 2, 4, 6, 8, and 10 are reverse scoring.Digital analytics, including the completion of sections from the intervention website will be used to measure patterns of engagement with the intervention components. These data will be collected at the 6-month follow-up and will be included in the evaluation of compliance level.

To be more specific, participants in the intervention group will be evaluated for compliance based on four categories: high compliance, moderate compliance, limited compliance and non-compliance, as summarised in Table 2. Highly compliant participants are those who complete at least 10 sections (66.66% or more) of the intervention, receive the supportive phone call, and set a personal goal with an action plan. Moderately compliant participants complete between 6 and 9 sections of the intervention and fulfil at least one secondary requirement, such as receiving the supportive phone call or setting a personal goal with or without an action plan. Limited compliant participants complete fewer than 5 sections (33.33% or less) but meet at least one secondary requirement. Participants who do not satisfy the criteria for a given category will be classified in the next lower level of compliance, with non-compliant participants being those who fail to meet the criteria for limited compliance.

**Table 2 Tab2:** Details for compliance levels

High compliance	Moderate compliance	Limited compliance	Non-compliance

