### Participants

#### Inclusion criteria

Patient participants will be eligible for inclusion if they (i) are adults ≥ 18 years; (ii) have been in an ICU for a minimum of 72 h; (iii) have required Level 3 care (failure of two or more organs and/or requiring advanced respiratory care) [21] during their ICU stay; (iv) self-report symptoms of fatigue at the point of discharge (± 7 days) from hospital (≤ 34/52) on the validated Functional Assessment of Chronic Illness Therapy-Fatigue (FACIT-F) additional concerns subscale [37]; (v) are ready for discharge from hospital (± 7 days); and (vi) are willing and able to comply with the study protocol requirements and procedures.

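### The printed FACIT-F reversal key appears to make high scores mean worse fatigue, while the ≤34/52 entry criterion needs low scores to mean worse

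*Protocol article*

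**What the plan says.** Two parts of the Protocol article bear on the direction of the FACIT-F fatigue score.

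- **Inclusion criteria.** A patient qualifies on a score "from hospital (≤ 34/52) on the validated Functional Assessment of Chronic Illness Therapy-Fatigue (FACIT-F) additional concerns subscale". Being at or below the threshold is what counts as fatigued, so low is worse.
- **Secondary outcome measures, FACIT-F entry.** The domains are "physical well-being, social/family well-being, emotional well-being, functional well-being, and fatigue". On responses: "Items are scored on a 5-point Likert scale from 0 (“not at all”) to 4 (“very much". The reversal key reads: "Questions GSs, GFs, An5, An7 are reverse scoring". No other item is listed as reversed. On the total: "Subscale scores are summed to produce a total score indicating the degree of fatigue and its impact on daily life".

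The article never says in words whether a higher FACIT-F score is better or worse, although it does state the direction for the WSAS in the same section.

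The Brief-COPE entry also lists reversals, "Question 6, 8, 11, 13, 16, and 26 are reverse scoring", on a scale where every item is rated by how often a strategy is used. It gives no reason for them.

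**The concern.** By their initials, GS and GF match the social/family and functional well-being domains. If those items are worded positively, as their domain names suggest, reversing them turns high into worse. Leaving most fatigue items raw, with the top response meaning very much, does the same for the fatigue subscale. The entry criterion needs the opposite direction on that subscale.

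Two things are at stake. The Data analysis section compares groups, and change between groups, to judge whether fatigue falls, so a score running against the entry scale would make improvement look like deterioration. And if the same key were programmed for screening, the cut-off would select the wrong end of the fatigue range. That would also reach the primary recruitment rate, whose denominator is restricted to eligible patients. The range checks described under Data management would not catch either error, because both directions give scores from 0 to 52.

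**Working it through.** **Inputs.** Cut-off 34 and maximum 52 (Inclusion criteria); items scored 0–4 and the reversal list (Secondary outcome measures). The number of fatigue items is not stated; 52 / 4 = 13 is consistent with 0–4 items but is inferred.

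**Assumption.** Item wording is not shown. I take the 11 unlisted fatigue items (13 − 2) to be symptom statements, where a high response means more fatigue, and An5 and An7 to be worded the other way.

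**Step 1: the two keys are mirrors.** Let L be the score that the cut-off needs (11 symptom items reversed, An5 and An7 raw) and P the score from the printed key (11 items raw, An5 and An7 reversed). Each item adds x to one score and 4 − x to the other, so L + P = 13 × 4 = 52, and P = 52 − L. A patient with maximum fatigue scores L = 0 and P = 11 × 4 + 2 × 4 = 52.

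**Step 2: the cut-off applied to each.** P ≤ 34 means 52 − L ≤ 34, so L ≥ 18.

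| Low-is-worse score L | Rule on L (≤34) | Rule on P (≤34) |
|---|---|---|
| 0–17 (most fatigued) | admitted | excluded |
| 18–34 | admitted | admitted |
| 35–52 (least fatigued) | excluded | admitted |

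Each rule admits 35 of the 53 possible scores, but only the 17 scores from 18 to 34 are admitted by both, and no score is excluded by both. These are counts of possible scores, not of patients.

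**Step 3: outcomes only.** If screening uses L and outcomes use P, a patient who enters at L = 10 has an outcome-scale score of 52 − 10 = 42. An improvement to L = 20 appears as 52 − 20 = 32, so a gain of 10 is recorded as −10. Group differences change sign in the same way.

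**Step 4: variability.** Var(52 − L) = Var(L), so the SD of the subscale is the same under both keys; a simulation with random item responses gave 5.10 for each. Correlations between visits scored with one key are also unchanged.

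**Step 5: does another wording remove the conflict?** Suppose the unlisted fatigue items were worded positively. The subscale would then agree with the cut-off, but reversed well-being items (high is worse) would be added to a fatigue part running the other way, and the total would have no single direction. The key is coherent with the cut-off only if the GS and GF well-being items are worded negatively and most fatigue items positively. Nothing in the article suggests that.

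**Step 6: Brief-COPE.** 14 subscales × 2 items = 28 items, split 10, 6 and 12 across the three dimensions. If one item of a pair were reversed, responses 4,4 and 1,1 would both score 5 (4 + 1 and 1 + 4). Six reversals cannot re-orient the whole 12-item dysfunctional dimension. The article does not map item numbers to subscales, so the check goes no further.

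**The case against.** The strongest reply is that the article nowhere states that a higher FACIT-F score is worse. The sentence on the total is neutral about direction and concerns the five-domain total, not the 52-point subscale used for entry. The mirror result rests on item wording that is not shown. This stands as a limit on certainty: the conflict is a strong inference, not a proof. It does not reduce the point to missing detail, because the article prints a key, and Step 5 shows that the only reading that rescues it is an implausible one.

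A reader might infer three stronger things that the document does not support.

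- **That the wrong patients are being enrolled.** The Inclusion criteria cite the validated subscale and do not refer to the key, which appears only among the outcome descriptions. Wrong entry is conditional on that key having been used at screening.
- **That the variability estimates for the future trial are spoiled.** Step 4 shows that they are not, for this subscale.
- **That the Brief-COPE reversals are wrong.** They are unexplained against a uniform frequency-of-use scale, but without item wording or an item-to-subscale map the document cannot show an error.

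It is also fair to say that recruitment and retention are the primary outcomes, that Table 1 uses counts and completion only, and that the article itself calls treatment-effect inferences tentative.

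**Conclusion.** The point holds for the FACIT-F. The printed key and the entry criterion appear to run in opposite directions, and the two sections must be reconciled. On the stated wording assumption the size is exact: the printed score is 52 minus the low-is-worse score. Used for outcomes only, this inverts the sign of fatigue changes and group differences and leaves their magnitude and the SD alone. Used at screening, it would shut out the most fatigued third of the score range (18 of 53 possible scores) and let in an equal number at the least fatigued end.

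The weight depends on which applies. If the key touches outcomes only, it should be corrected before analysis but threatens neither the progression decision nor the variability objective. If it was used at screening, it becomes essential, because eligibility and the recruitment rate are then affected. For the Brief-COPE, the conclusion is only that the listed reversals need checking.

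**What to change.** 1. Replace the printed FACIT-F key with one under which higher means less fatigue, consistent with the ≤34/52 criterion: reverse the symptom-worded items and leave the GS, GF, An5 and An7 items unreversed. Check every item against the instrument's scoring manual before adopting it.
2. State that direction once, for both eligibility and outcome, in the Inclusion criteria and in the FACIT-F entry.
3. Test the REDCap scoring with an all-0 and an all-4 record. On the 13-item assumption, the corrected fatigue subscale should return 11 × 4 + 0 = 44 and 0 + 2 × 4 = 8; the printed key would return 8 and 44.
4. Confirm and document which direction was used for patients already screened.
5. Check the six Brief-COPE reversals against its manual, and either give the reason for them or remove them.

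The cost is a short text correction, a scoring-code change and two test records. Outcome data can be re-scored if item responses are held. An entry decision made on the wrong direction cannot be undone, so step 4 should come first.

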### Intervention

The FACT self-management intervention is based on the common-sense model of self-regulation [23] and consists of four structured modules covering aspects of fatigue management, including (i) About fatigue; (ii) Managing your energy with the 5 Ps (Priorities, Pacing, Planning, Permission, Position); (iii) Strategies for everyday life; and (iv) Goal setting and making plans. The intervention is separated into 16 sections and includes information in the form of both videos and text, activities, as well as patient stories. It is available via a website with all information and activities available to download and accessible in multi-formats (infographics, videos, printable and editable documents). A printed booklet will also be available according to patient preferences.

Patients will be encouraged but not required to move through the topics in the order presented and will be able to use the intervention at their own pace, repeating any topics if desired. As described in “Trial Design”, participants will receive a 30-min supportive phone or video call with an HCP from the ICU follow-up team at three months post-discharge. During this call, the HCP will assist with goal setting and action planning. To ensure consistency and quality of delivery, HCPs will attend an online training session and follow a defined protocol. In addition, a manual for research delivery nurses has been developed, which includes a clear timeline and action checklist to guide screening, recruitment, and participant follow-up. To support the delivery of the intervention, supportive call materials have also been prepared, including a supportive phone call structure and example scripts to help HCPs conduct the phone calls effectively and maintain fidelity to the intervention framework.

The control arm will receive usual care across all the research sites; existing inpatient ICU follow-up services are offered. These include inpatient ICU follow-up services, and patients who were in ICU for more than 72 h are offered outpatient services three months after hospital discharge, where physical and psychological health outcomes are evaluated. Where necessary, appropriate referrals and treatment plans are made. In addition, patients may also have access to generic information about recovery after critical illness available on a variety of websites (ICU Steps, criticalcarerecovery.com), which includes information about fatigue.

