**Mandatory requirement**			
Participant has accessed and completed 10 (66.66%) or more sections from the intervention (including goal setting and action planning section)	Participant has accessed and completed more than 5 but less than 10 of the sections from the intervention (including goal setting and action planning section)	Participant has accessed and completed fewer than 5 (33.33%) of the sections in the intervention **or** has not completed the goal and action planning section	Participant does not fulfil the necessary conditions to be considered as **Limited compliant**

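### Website analytics are the only source named for section completion although a printed booklet is offered, so adherence of booklet-only participants could be understated

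*Protocol article*

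**What the plan says.** **Formats.** The Intervention section of the protocol article describes more than one way to use the material. On the website it says: "It is available via a website with all information and activities available to download and accessible in multi-formats". It then adds: "A printed booklet will also be available according to patient preferences". On the size of the programme: "The intervention is separated into 16 sections".

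**Source of the section count.** Under Secondary outcome measures the article states: "Digital analytics, including the completion of sections from the intervention website will be used to measure patterns of engagement with the intervention components". The next sentence reads: "These data will be collected at the 6-month follow-up and will be included in the evaluation of compliance level". The compliance categories follow directly. No booklet log, self-reported section count or separate rule for booklet users is described. The Aims and objectives also express fidelity partly through how often the website is visited.

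**Rule.** Table 2 sets a mandatory section requirement. For High it is: "Participant has accessed and completed 10 (66.66%) or more sections from the intervention". For Moderate it is: "Participant has accessed and completed more than 5 but less than 10 of the sections from the intervention". Both must include the section on goals and action plans. The supportive call and a personal goal are secondary requirements. A participant who fails one level drops to the next lower one.

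**The concern.** Offline use is an intended mode of delivery, chosen by the patient, but the one source named for the mandatory criterion sees only the website. Under that source, not using the material and using it on paper look the same.

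Adherence and fidelity belong to a stated secondary objective, and the findings are meant to shape the full trial. An error here runs in one direction, towards lower adherence. It also cannot be repaired later, because offline use that was never recorded cannot be recovered at analysis. Low recorded compliance might then be read as patients not using an intervention that some of them did use.

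**Working it through.** **Inputs from the protocol article**
- 70 participants allocated 1:1, so 70 / 2 = 35 in the intervention arm (Study design).
- 16 sections (Intervention).
- High: at least 10 sections including goal setting, plus the call, plus a goal with an action plan. Moderate: 6 to 9 sections including goal setting, plus the call or a goal. Limited: fewer sections, or the goal section not completed, plus the call or a goal. Otherwise Non-compliant (Secondary outcome measures and Table 2).
- Share of participants using only the booklet: not given.

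**Step 1. The plan's own figures.** Table 2 equates 10 sections with 66.66% and 5 with 33.33%. With 16 sections, 10/16 = 62.5% and 5/16 = 31.25%. The printed percentages need 15 sections: 10/15 = 66.67% and 5/15 = 33.33%. This is a separate matter. The check below uses the counts, not the percentages.

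**Step 2. Table 2 applied twice to the same person.** Take a booklet-only participant who in truth completed all 16 sections. Classify once with true use, and once with the 0 sections that website analytics would show.

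| Call received | Goal set | Action plan | 16 sections counted | 0 sections counted |
|---|---|---|---|---|
| no | no | no | Non-compliant | Non-compliant |
| no | yes | no | Moderate | Limited |
| no | yes | yes | Moderate | Limited |
| yes | no | no | Moderate | Limited |
| yes | yes | no | Moderate | Limited |
| yes | yes | yes | High | Limited |

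Five of the six combinations move down. With no sections logged, High and Moderate cannot be reached. The call and the goal cannot make up for this, because they are secondary to the section requirement. A participant with neither is Non-compliant under both counts.

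**Step 3. Illustration of size (assumed inputs).** Let *b* be the booklet-only share and *p* the true proportion with High or Moderate compliance, the same in both formats. If no booklet-only participant has a section logged and web users are classified correctly, then

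recorded proportion = *p* × (1 − *b*).

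With *p* = 0.70:
- *b* = 0.10: 35 × 0.10 = 3.5 people cannot exceed Limited; recorded 0.70 × 0.90 = 0.63, a loss of 7 percentage points.
- *b* = 0.40: 35 × 0.40 = 14 people cannot exceed Limited; recorded 0.70 × 0.60 = 0.42, a loss of 28 percentage points.

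The people actually moved down number 35 × 0.07 = 2.45 to 35 × 0.28 = 9.8, so about 2 to 10. Both *b* and *p* are assumptions. Under the stated conditions the direction does not depend on them; the size does.

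**The case against.** The strongest reply is that the rule itself does not depend on format. Table 2 counts sections of the intervention, not of the website. The analytics are one contribution to the compliance level and are not called its only basis. Nothing says that a participant without web data is counted as zero. The article is a condensed text: Table 3 is not shown, and neither is the manual for research delivery nurses, so booklet capture may be defined elsewhere. Interviews at six months are also meant to cover adherence.

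Much of this stands, and it limits the point. A reader might infer any of the following, but the documents do not support them:
- *That offline users will certainly be scored zero.* This follows only if the named source is used alone.
- *That downloaders are lost in the same way as booklet users.* Downloads are obtained from the website and may leave a trace. How a section is logged as completed is not defined, so under-counting is possible but a zero is not established.
- *That comparisons between compliance levels will be biased, or that paper users differ in age, cognition or digital access.* No such comparison is described in the text shown, and the article says nothing on who prefers paper.
- *That the decision to proceed is at risk.* Table 1 uses recruitment and retention only.

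What the reply does not remove is the mismatch. The article sets out source, thresholds and downgrading in some detail, and the one source it names cannot see a format that it offers. The interviews are qualitative, follow an acceptability topic guide and are not tied to a section count.

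**Conclusion.** The point holds in conditional form. If website analytics are the sole source for section completion, booklet-only participants who took the call or set a goal can be classed no higher than Limited, however much they used. Those who download material may be under-counted. Adherence would be understated.

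The amount cannot be computed, because booklet uptake is not stated. The fall from 70% to between 63% and 42% shows only what assumed shares of 10% to 40% would do. The consequence is confined to a descriptive secondary outcome. It is worth correcting because the correction is cheap and the lost information cannot be recovered afterwards.

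**What to change.** 1. Record for each intervention participant which formats were used: website, download, booklet or a mix.
2. At the existing six-month assessment, ask intervention participants to tick which of the 16 sections they completed, with the goal-setting section identifiable. Keep this out of the three-month supportive call. That call is part of the intervention, and a checklist there could prompt the use being measured.
3. Apply Table 2 to analytics and checklist combined, and state beforehand how the two are merged, for example that a section counts if either source shows it.
4. Report compliance by format as well as overall.
5. Where use could not be seen on the web and no self-report exists, treat the section count as missing, not zero.

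If the full protocol or the manual already provides for booklet users, a sentence naming that source would settle the capture question.

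The cost is one short checklist at a contact that already takes place. The downside is reliance on self-report, with recall over six months, for offline users. Asking web users the same list would show how far self-report and analytics agree.

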**Secondary requirements**			
**(Need to satisfy both or assessed as moderately compliant)**	**(Need to satisfy at least one or assessed as limited compliance)**	**(Need to satisfy at least one or assessed as non-compliant)**	
Participant has received the supportive phone call	Participant has received the supportive phone call	Participant has received the supportive phone call	Participant has not received the supportive phone call
Participant has set a personal goal and devised an action plan	Participant has set a personal goal (with or without an action plan)	Participant has set a personal goal (with or without an action plan)	Participant has not set a goal or an action plan

In addition to quantitative measures, the acceptability of the intervention will be assessed through semi-structured interviews with participants to assess their adherence and provide further understanding of feasibility in the sixth month. Semi-structured interviews of health professionals are also included to evaluate HCPs’ perceptions and experiences of delivering support in this intervention. Topics will include affectivity, burden, ethicality, perceived effectiveness, intervention coherence, self-efficacy, opportunity costs, and general acceptability. These interviews will use a topic guide based on the theoretical constructs of acceptability [31].

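### The text and Table 2 disagree on whether the web goal-setting section is required for High or Moderate compliance, so the same participant can be High by one and Limited by the other

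*Protocol article*

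**What the plan says.** The text under Secondary outcome measures defines the levels by the number of sections completed plus secondary requirements (the call, and a personal goal with or without a plan).

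- High: "Highly compliant participants are those who complete at least 10 sections (66.66% or more) of the intervention, receive the supportive phone call", and who also set a personal goal with an action plan.
- Moderate: "Moderately compliant participants complete between 6 and 9 sections of the intervention and fulfil at least one secondary requirement".
- Limited: "Limited compliant participants complete fewer than 5 sections (33.33% or less) but meet at least one secondary requirement".
- Stepping down: "Participants who do not satisfy the criteria for a given category will be classified in the next lower level of compliance". The lowest level is what remains when the Limited definition is not met.

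None of these definitions names a section that must be among those completed.

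Table 2, to which the text refers as the summary of the same categories, has two layers. Its mandatory row requires the section count to include goal setting and action planning, for both High and Moderate. Its Limited column takes in a participant with fewer than 5 sections or, as an alternative, one who "has not completed the goal and action planning section". Its secondary rows then deal separately with the call and with having set a goal. The High column there carries the note "Need to satisfy both or assessed as moderately compliant"; the Moderate and Limited columns carry matching notes that each drop the participant one level if neither secondary requirement is met.

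**The concern.** Two statements of one rule should give one answer for every participant. Here the table contains a requirement that the text lacks, and neither document section says which prevails.

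The participants on whom they differ are those who complete several web sections but not the goal-setting one. The Intervention section shows how that can happen: goal setting is the fourth of four modules, "Patients will be encouraged but not required to move through the topics in the order presented", and the healthcare professional helps with goals and action plans during the call. A goal and plan can therefore exist without the web section having been completed.

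Adherence is part of the secondary objective on acceptability and fidelity (Aims and objectives), and the four levels are how the protocol grades compliance. As written, the reported distribution depends on whether the analyst codes from the text or from the table.

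**Working it through.** **Inputs.** 16 sections (Intervention); 70 participants randomised 1:1, so 70/2 = 35 in the intervention arm (Study design, Sample size); the level definitions from the text and Table 2 as set out above.

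**The plan's own percentages.** The protocol equates 10 sections with 66.66% and 5 sections with 33.33%. With 16 sections, 10/16 = 62.5% and 5/16 = 31.25%. The printed figures fit 15 sections (10/15 = 66.67%, 5/15 = 33.33%). This is a separate slip. The profiles below use section counts, so nothing here depends on it.

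**Profiles run through both rules.**

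| Profile | Text | Table 2 |
|---|---|---|
| A. 12 sections, goal section not completed; call received; goal and plan set | High | Limited |
| B. 8 sections, goal section not completed; at least one secondary requirement met | Moderate | Limited |
| C. 12 sections, goal section completed; no call, no goal | Moderate if stepped down once; Non-compliant if stepped down in turn | Same two outcomes |

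*Profile A.* Text: 12 is at least 10, the call was received, and a goal and plan were set, so High. Table 2: the mandatory row for High fails because the goal section is missing; the mandatory row for Moderate fails for the same reason; the Limited column is met through its alternative condition, and its secondary requirement is met by the call. Result: Limited, two levels lower. The result is the same for any count from 10 to 15 without that section.

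*Profile B.* Text: 8 lies in 6 to 9 and one secondary requirement is met, so Moderate. Table 2: the mandatory row for Moderate fails, and the Limited column is met. Result: Limited, one level lower.

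*Profile C.* There is no disagreement between text and table here. The participant meets the mandatory row for High but neither secondary requirement. The note in the High column, taken alone, gives Moderate. Checking each category in turn gives: Moderate needs at least one secondary requirement (none met), Limited needs at least one (none met), so Non-compliant. The Non-compliance column of Table 2 describes this participant on both secondary rows: no call, and no goal or plan.

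**Why the counts need to be minimums.** Take 12 sections including the goal section, the call received, and a goal without a plan. High fails, and both sources step the participant down to Moderate. Yet 12 lies outside the Moderate range of 6 to 9. Stepping down works only if that range is read as 6 or more.

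**Size per participant.** 1/35 = 0.0286, about 2.9 percentage points of the arm for each person who changes category.

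**The case against.** The best defence of the plan is that the text points to Table 2, whose title promises the details, and is merely silent on the goal-setting section. An analyst who codes from the table gets one answer for profiles A and B: Limited. That is a reasonable working convention, but the protocol does not state it, and the text is phrased as a definition of who is highly compliant, not as an outline. Nor can setting a goal be equated with completing the section: Table 2 lists the section as a mandatory requirement and the goal as a separate secondary one.

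On stepping down, the defence largely succeeds. A reader might infer that text and table have different step-down rules, or that profile C has no determinate level anywhere between Moderate and Non-compliant. The documents do not support that. The one-level wording is common to both, Limited is only an intermediate step, and applying the criteria in turn agrees with the fourth column of Table 2. What stands is that the note in the High column misleads if it is applied once and left there.

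The consequences are also bounded. Compliance level is descriptive and concerns one arm. The Data analysis section specifies intention-to-treat and describes no analysis by compliance; the analysis summary in Table 3 is not reproduced in the text available. Section completion is captured by website analytics, so levels can be re-derived later. Acceptability also draws on two questionnaires and the interviews.

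**Conclusion.** The contradiction on the goal-setting section is real and needs no interpretation: profile A is High by the text and Limited by Table 2, and profile B is Moderate by the text and Limited by Table 2. The step-down wording is a lesser ambiguity, shared by both.

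The effect is about 2.9 percentage points per reclassified participant, assuming the planned 35 in the intervention arm. Three larger inferences should be resisted:

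- That a large share of the distribution is at stake. The documents give no basis for the number of participants with these profiles.
- That the ambiguity puts an engaged participant on a level with anyone who never used the website. No sections plus the call is Limited, not Non-compliant, under both rules.
- That the decision to proceed is affected. Table 1 uses recruitment and follow-up completion only.

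The wording should be settled before anyone is classified, because the adherence result is one that a future trial would draw on.

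**What to change.** 1. State one rule and print it identically in the text and in Table 2. Say whether the web goal-setting section is mandatory for High and Moderate, or whether a goal set on the call also satisfies the requirement, and delete the other version.
2. Replace the step-down wording in both places, including the notes in the Table 2 columns, with a single instruction: assign the highest level whose mandatory and secondary requirements are all met, treating the section counts for High and Moderate as minimums.
3. In the same edit, give a count of exactly 5 a place. Moderate starts above 5 and Limited is below 5, so the bands leave it out.
4. Report the components alongside the level: sections completed, goal section completed, call received, goal set, action plan set. This lets a reader rebuild the classification under another rule.

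The cost is wording in the protocol and Table 2. It needs no additional participants and no new data, since the level cannot be assigned under Table 2 without these components.
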